### Participants

The study will include typically developing kindergarten children aged 3–5 years. Children aged 6 years will be excluded to avoid attrition due to their transition to primary school. The inclusion criteria are as follows: (1) Participants must be aged between 3 and 5 years (preschoolers). (2) Participants must attend a kindergarten in each of the 18 administrative districts in Hong Kong. (3) Participants must be free of any illness or disability that might interfere with their ability to complete the FMS, physical activity, daily tasks, or cognitive tasks required for the intervention. (4) Prior to enrollment in the intervention, informed consent signed by a parent or guardian must be obtained. The exclusion criteria are as follows: (1) Participants out of the age range of 3–5 years. (2) Participants who cannot attend kindergarten regularly. (3) Participants with known medical conditions or disabilities that would limit their participation in completing the FMS, physical activity, daily tasks, or cognitive tasks required for the study intervention and assessments. (4) Participants who did not provide consent from their parents or guardian.

### Sample size calculations

The sample size is calculated using G*Power version 3.1, which is based on the assumed effect size and dropout rates. In a previous systematic review, the effect size of using FMS alone or cognitive challenges alone as an intervention was medium, whereas the effect size of combined FMS and cognitive challenges ranged from small to large [8]; thus, we assumed that the effect size for the current intervention would be medium (f = 0.3), α = 0.05, and power = 0.80, resulting in a total sample size of at least 82 young children [42]. Additionally, we assumed a participant dropout rate of 20%, resulting in a total sample size of at least 103 young children. This study is a four-arm cluster randomized crossover trial that will involve 18 kindergartens from different districts, and it is estimated that there will be 11 children in each class, so the total number will be 18*4*11 = 792, which meets the minimum requirement of the required sample size.

### Intervention strategy

The AMPLE program comprises four intervention arms:aCombination Group (FMS with cognitive challenge)A series of FMS games with cognitive challenges will be implemented by trained teachers during classroom time. Each game will last 30 min and will be played 3 times a week for a total of 3 weeks. An example of a game with cognitive challenges running as FMS training: “connect 4 real version”, a board with 7 columns and 6 rows, 1.2 m long and 1 m wide, will be placed, with all participants standing behind a taped line 15 m away and a timer set for 30 min. The goal of the participants is to place their 4 game pieces on the large board as quickly as possible and keep the pieces in a straight line (horizontal, vertical, or diagonal lines are all allowed). The game is played in pairs, and once a participant has placed their piece and run back behind the tape line, the next participant is allowed to begin [19]. Throughout the game, all participants will be monitored for heart rate to ensure that their heart rate is maintained within 65% to 85% of their maximum heart rate.bCognitive Group (Sedentary with cognitive challenge).A series of games with only cognitive challenges will be implemented by teachers during classroom time. Each game will last 30 min and will be played 3 times a week. An example of the game is “connect 4 routine version”, all participants will be seated at a table to ensure a sedentary state, and a timer will be set for 30 min. The goal of the game is to place 4 of their own game pieces on the board and try to connect the pieces in a straight line. The game is played in pairs, and once one participant has placed his or her piece, the other participant will be allowed to place the piece.cPhysical Group (FMS without cognitive challenge).A series of games with FMS interventions will be implemented by the teachers during classroom time. Each game will last 30 min and will be played 3 times a week. An example of the game is as follows: a clearly marked chart with rounds will be placed, all participants will stand behind a taped line 15 m away, and a timer will be set for 30 min. Once a participant has run out, they need to mark the number of rounds on the chart as soon as possible and return; once they have returned, the next participant is allowed to start and repeat. Throughout the game, all participants will be monitored for heart rate to ensure that their heart rate remains within 65% to 85% of their maximum heart rate.dControl Group (Sedentary without cognitive challenge).All participants will not engage in any cognitive challenge or FMS interventions but will sit in their own seats while the teacher plays a 30-minute story appropriate for young children. All participants will be informed prior to the start of the program that they will not be asked any questions related to the video or story and ensure a state of minimal cognitive engagement.

### Washout period

In a cluster randomized crossover (CRXO) design, washout periods need to be carefully set to minimize the impact of the effects produced by the previous intervention on the next intervention [43]. The carry-over effects of psychological or behavioral interventions are difficult to measure accurately, and the optimal duration for a washout period has not yet been clearly established. In a study published by a team of Stanford University researchers on the effects of digital physical activity intervention on daily steps, the crossover process of four interventions did not have a washout period [44]. Some previous crossover designs related to PA interventions agreed that it is appropriate to set a washout period equal to the duration of the intervention period [45–47]. In addition, there is a need to consider the impact of young children’s own rapid development of motor skills and cognition in non-intervention situations. Therefore, this study hypothesizes that the carry-over effects of the intervention on young children will be greater than the rest of the lifespan, that the duration of the washout period will be set to be twice the length of the intervention period (3 weeks for the intervention period and 6 weeks for the washout period), and that pre-tests and post-tests will be implemented at each stage of the intervention to ensure the accuracy of the measurements

### Data collection procedures

Data collection will follow a cyclical pattern: 1-week pre-test, 3-week intervention, 1-week post-test, and 6-week washout. This cycle will be repeated three times, followed by a final post-test at week 38 and three follow-up tests at 8-week intervals (weeks 46, 54, and 62). See Table 1 for the detailed schedule. In the CRXO design of this study, from the cohort perspective, each cluster is required to receive all 4 interventions sequentially; from the cross-sectional perspective, each cluster is required to receive 4 different interventions each at the same time; thus, a total of 24 combinations of the intervention sequence are generated (4*3*2). Since the effect of the intervention sequence on the results of the study will not be considered, this study will use GraphPad Software to randomly select the combination of the intervention sequence to be used in the study.

**Table 1 Tab1:** Schedule of the cluster randomized crossover trial

Schedule of Interventions 2025–2026		
20/10/2025-26/10/2025	1 week	Pre-test 1
27/10–16/11	3 weeks	Intervention 1
17/11–23/11	1 week	Post-test 1
24/11/2025-4/1/2026	6 weeks (Including Public Holiday for Christmas)	Washout period 1
5/1–11/1	1 week	Pre-test 2
12/1–1/2	3 weeks	Intervention 2
2/2–8/2	1 week	Post-test 2
9/2–22/3	6 weeks (Including Public Holiday for Spring Festival)	Washout period 2
23/3–29/3	1 week	Pre-test 3
30/3–19/4	3 weeks	Intervention 3
20/4–26/4	1 week	Post-test 3
27/4–7/6	6 weeks	Washout period 3
8/6–14/6	1 week	Pre-test 4
15/6 − 5/7	3 weeks	Intervention 4
6/7–12/7	1 week	Post-test 4
13/7 − 6/9	8 weeks (13/7–31/8 for washout, 1/9 − 6/9 for test)	Follow-up 1
7/9 − 1/11	8 weeks (7/9–25/10 for washout, 26/10 − 1/11 for test)	Follow-up 2
2/11–24/12	8 weeks (2/11–17/12 for washout, 18/12–24/12 for test)	Follow-up 3

The intervention period starts on October 20, 2025, and ends on July 12, 2026, lasting for 38 weeks (10 months). Kindergartens in Hong Kong have Christmas holidays in late December, traditional Chinese New Year holidays in mid-February, and summer vacations in mid-July. As a result, this study will put relatively long vacation periods in the washout period to ensure that all interventions and assessments could be completed in the kindergarten. In addition, in September, teachers may not be familiar with the newly enrolled children, and young children may not yet fully adapt to kindergarten life. Attrition is considered to appear during this period. Thus, the study will start in late October to ensure the smooth implementation of the intervention.

Data will be collected through a combination of objective measures and questionnaires and direct observation during the pre-test, post-test and follow-up test periods (see Fig. 1). In addition to professionally trained test evaluators, kindergarten principals and teachers will play an important role in the study. The principal will be the main contact person for the implementation of the study and will be responsible for approving and monitoring the full process of compliance with the program. Teachers in the relevant classrooms will be invited to participate in weekly workshops held by the research team until the end of the intervention. During the workshops, teachers will be carefully instructed on the carefully designed intervention plan for the following week for the different groups, dos and don’t, safety guidelines, etc., as well as how to use, fill out, and keep the evaluation booklet in between interventions. The attendance of all participating teachers will be recorded, which is considered to be one of the important factors that may affect the effectiveness of the intervention. Except for the kindergarten principal, teachers and children will be blinded to the differences in intervention strategies throughout the process, and all assessors will be blinded to group assignment. Unblinding will be permissible after the end of the project.

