**Methods:**

This program integrates fundamental movement skills training with cognitively challenging activities. Four classes per kindergarten will be randomly assigned to one of four conditions: (1) combined fundamental movement skills and cognitive challenge, (2) sedentary with cognitive challenge, (3) fundamental movement skills alone, or (4) sedentary without cognitive challenges. Each condition involves 30-minute sessions, three times per week, with a six-week washout period between the three-week intervention phases. The research team will use multiple objective measures and self-report measures, covering the elements and domains of the assessment of physical literacy and executive function. Three follow-up tests will be conducted within six months after the end of the intervention to evaluate the long-term impact of the program. Intervention implementation and fidelity will be assessed through focus group interviews with teachers and principals.

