### Data analysis

Descriptive statistics (means and standard deviations) will be calculated for all subscales across all measurements. Missing data will be calculated via maximum likelihood estimation via SAS version 9.4 (Cary, NC, USA). Given the characteristics of behavioral intervention research, we will not assume that the collected data will conform to a normal distribution and will be independent of each other. Therefore, a linear mixed effects (LME) model (from the R library NLME, R version 3.4.4) will be used to analyze the associations of different interventions with EF. The number of intervention days (time) was considered to have a possible association with intervention effects [72], so the interaction between the two will be included in the model. Fixed effects will include the intervention days and group, whereas the cluster (i.e., kindergarten) will be treated as a random effect. The LME model will be generated via the R NLME package. A p value less than 0.05 is recognized as a significant difference. Tukey’s honestly significant difference (HSD) test will be used to determine whether there is a significant difference between the interventions [73]. In addition, the false discovery rate-corrected *p* value will be used to determine if there is a statistically significant difference between the interventions. A value less than 0.05 is considered significant. Secondary outcomes (including cognitive difficulty, PA intensity, and teacher attendance) will be similarly assessed via the LME model.

An exploratory factor analysis of the possible static associations between FMS and EF will be conducted, which will be analyzed via partial least squares structural equation modeling (PLS-SEM), since PLS can maximize the prediction capability [74] and can address formative indicators as well as reflective indicators [75]. The relationship between PL and EF will be assessed via Pearson’s correlation coefficient. The effect size (Cohen’s *d*) will be calculated by dividing the difference between the post-intervention means of the two groups by their pooled standard deviation (SD).

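### The plan sets sequence effects aside and lists no term for carry-over or the period pre-test, although it expects carry-over and effects that outlast the washout

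*Protocol article*

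**What the plan says.** All references are to the protocol article.

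- **Choice of order.** Data collection procedures describes four conditions taken in turn by each cluster and also running in parallel: "each cluster is required to receive 4 different interventions each at the same time". It counts the possible orders: "thus, a total of 24 combinations of the intervention sequence are generated (4*3*2"). The order is then settled by software. The reason given is "Since the effect of the intervention sequence on the results of the study will not be considered", and the software will "randomly select the combination of the intervention sequence to be used in the study".
- **Carry-over.** Washout period hypothesises that "the carry-over effects of the intervention on young children will be greater than the rest of the lifespan". It therefore sets a 6-week washout after each 3-week intervention and adds that "pre-tests and post-tests will be implemented at each stage of the intervention to ensure the accuracy of the measurements". It also names the children's own rapid development as a concern.
- **Duration of effect.** The Background states H1 to H5 for the time after both intervention and follow-up. The abstract says: "Three follow-up tests will be conducted within six months after the end of the intervention to evaluate the long-term impact of the program". The schedule ends the last post-test at week 38 and tests again at weeks 46, 54 and 62.
- **Analysis.** Data analysis lists intervention days, group and their interaction as fixed effects, and kindergarten as the random effect. Cohen's d comes from "dividing the difference between the post-intervention means of the two groups by their pooled standard deviation".
- **Limitations.** Strengths and potential limitations accepts that carry-over may occur and that no evidence establishes the best washout length.

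**The concern.** A crossover comparison made without regard to sequence is unbiased only if the previous condition has left no trace by the time the next is measured. The plan does not claim this, and three of its own statements point the other way: carry-over is expected to be greater in this age group, effects are hypothesised at follow-up, and the washout is unproven. Yet it states as a rule that sequence will be disregarded, and it lists no model term that could detect or absorb a carried-over effect. A pre-test is taken in every period, but the stated effect size does not use it.

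Two things are at stake. First, any residual effect pulls the condition contrasts together on average, because the control condition is always preceded by something active except in period 1. Second, if few distinct arrangements are used, a contrast also reflects which condition happened to come before which. Combination versus FMS alone is the contrast most exposed to this. The Discussion presents it as the test of the cognitive engagement hypothesis, and it is likely to be small.

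**Working it through.** **Inputs from the article:** 4 conditions, 4 periods, 4 classes in each of 18 kindergartens; 3-week interventions; 6-week washouts; post-test means as the effect-size scale.

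**Assumed, because the article gives no figures:** effects of 0.40 (combination), 0.25 (cognitive), 0.25 (physical) and 0 (control) SD. A fraction ρ of the preceding condition's effect is still present at the next post-test, with ρ = 0.25 or 0.50. Only the immediately preceding condition carries over.

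**1. The plan's own count.** 4! = 4×3×2×1 = 24 orders for one class. It reproduces.

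**2. Timing.** From the end of one intervention to the next post-test is 1 + 6 + 1 + 3 = 11 weeks. Follow-ups come at 46−38 = 8, 54−38 = 16 and 62−38 = 24 weeks after the last post-test. An effect that is still present at the second or third follow-up would also have been present at the next period's post-test.

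**3. Arrangements.** Four classes holding four different conditions in each of four periods form a 4×4 Latin square. Enumeration gives 576 squares:
- 144 are Williams-balanced (each condition follows each other condition once);
- 288 are mixed;
- in 144, each condition always follows the same other condition.

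**4. Average bias.** In a balanced square each condition occurs four times: once in period 1, and once after each of the others. With S the sum of the four effects, condition a receives a mean carry-over of ρ(S − τa)/4. A contrast a − b is therefore changed by −ρ(τa − τb)/4, so it is multiplied by 1 − ρ/4 whatever the effects are.
- Combination minus control: 0.40 × 0.9375 = 0.375 (ρ = 0.25); 0.40 × 0.875 = 0.35 (ρ = 0.50).
- Combination minus physical: 0.15 × 0.9375 = 0.141; 0.15 × 0.875 = 0.131.

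The mean over all 576 squares is the same. Balance alone does not remove this attenuation.

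**5. Bias from the particular square, if one square serves the whole trial.** For combination minus physical (true 0.15):
- Lowest: combination always follows control and physical always follows combination. The change is −ρ × 3 × 0.40/4 = −0.30ρ, giving 0.075 (ρ = 0.25) or 0.00 (ρ = 0.50).
- Highest: combination always follows physical and physical always follows control. The change is +ρ × 3 × 0.25/4 = +0.1875ρ, giving 0.197 or 0.24.

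**6. The same, if each kindergarten draws its own square.** The draw-to-draw SD for one square is 0.028 (ρ = 0.25) or 0.057 (ρ = 0.50). Divided by √18, it is 0.007 or 0.013.

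**7. Cost of adjusting later.** This is the least-squares variance of combination minus control per square, with class and period in the model, in units of the residual variance:

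| Model | Williams square | Cyclic square |
|---|---|---|
| No prior-condition term | 0.50 | 0.50 |
| Prior-condition term added | 0.55 | 2.75 |

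Adjustment costs 10% in a balanced square (0.55/0.50) and multiplies the variance by 5.5 in a cyclic one (2.75/0.50).

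**8. Period.** In any complete Latin square each condition appears once in each period. A linear trend across periods then gives zero bias in every contrast.

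**The case against.** The design does address carry-over. The expectation of greater carry-over is the stated reason for a washout twice the intervention length and for testing before and after every period, and the limitations section is open about the residual risk. The gap is in the allocation rule and the analysis. Cohen's d is also a descriptive measure, with inference resting on the mixed model, and an article may leave the handling of pre-tests to a fuller analysis plan. That is fair, but a stated decision to disregard sequence is not an omission that a later plan merely fills in.

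Four stronger readings are tempting and are not supported.

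- **The key contrast could land anywhere from 0.00 to 0.24.** This needs one square for all 18 kindergartens and half of each effect carried over. The text does not say whether one arrangement or many will be drawn. With 18 independent squares the draw contributes an SD of only 0.007–0.013.
- **Omitting period biases the contrasts.** If the four classes of a kindergarten always hold different conditions, as the section on data collection suggests, the omission costs precision only. The intervention-days term may also absorb some time effect, though it is not defined as period.
- **The figure 24 is wrong.** It is the correct number of orders for one class.
- **The plan predicts strong carry-over.** It says greater, and gives no size.

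The follow-up argument is also partly inference. By then every class has had all four conditions, and the abstract speaks of the impact of the programme as a whole. The tension remains because H1 to H5 are between-group statements that explicitly cover follow-up.

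**Conclusion.** The point holds as an inconsistency between a stated rule and the plan's own premises. It should be fixed, but it does not undermine the trial.

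The robust part of the bias is modest and runs towards no difference. On average, unadjusted contrasts lose ρ/4 of their size, that is 6.25% at 25% carry-over and 12.5% at 50% (combination minus control 0.375 or 0.35 for a true 0.40). Bias specific to the sequence drawn is material only if a single arrangement, or very few, serves the whole trial. The article should close that possibility. An unlucky single draw would also make later adjustment expensive.

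All sizes rest on assumed effects, additive carry-over from the preceding condition only, and a carried-over fraction that the documents do not give. If nothing survives the 11 weeks to the next post-test, there is no bias.

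**What to change.** 1. Delete the statement that sequence will not be considered, and say whether one arrangement is drawn for the trial or one for each kindergarten.
2. If allocation has not been made, randomise each kindergarten to a Williams-balanced 4×4 square and randomise its four classes to the rows. This is still a random choice of sequence. It removes dependence on the particular draw and keeps later adjustment cheap, but it does not by itself remove the average attenuation.
3. Put the same-period pre-test and period (1 to 4) in the main model. Period is there for precision. The pre-test is there to take up what remains of the previous condition. How much attenuation it removes depends on how carry-over fades between pre-test and post-test, and was not calculated here.
4. Base Cohen's d on the pre-test-adjusted difference.
5. Pre-specify two sensitivity analyses: one that adds prior condition, and one that uses period 1 only. The second is free of carry-over and compares 18×4/4 = 18 classes per condition. It is imprecise, because with one class per condition in each kindergarten the contrast variance is at least 2 units against 0.50.

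The cost is a regenerated allocation list, analysis wording, and about 10% more variance in the prior-condition analysis under balanced squares. No extra children, visits or tests are needed. If allocation is already done, items 1, 3, 4 and 5 still apply, with item 1 then reporting the arrangement actually used.

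### Follow-up 3 is tested on 18-24 December, in the late-December period when the protocol says kindergartens have holidays, and its block is 53 days against a labelled 8 weeks

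*Protocol article*

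**What the plan says.** All of the following is in the protocol article, under Data collection procedures, unless another section is named.

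- **Follow-up dates (Table 1).** Follow-up 1: "13/7–31/8 for washout, 1/9 − 6/9 for test". Follow-up 2: "7/9–25/10 for washout, 26/10 − 1/11 for test". Follow-up 3: "2/11–17/12 for washout, 18/12–24/12 for test". Each block is labelled 8 weeks.
- **Spacing (text).** The plan is for "three follow-up tests at 8-week intervals (weeks 46, 54, and 62").
- **Holiday rule (text).** "Kindergartens in Hong Kong have Christmas holidays in late December", with further holidays in mid-February and from mid-July. Long vacations are therefore put in washout "to ensure that all interventions and assessments could be completed in the kindergarten". No closing or reopening dates are given.
- **September (text).** In that month "teachers may not be familiar with the newly enrolled children, and young children may not yet fully adapt to kindergarten life", and attrition is expected. The conclusion drawn is that the study starts in late October.
- **Accelerometer (Measurement of physical activity).** At least 8 hours a day on 6 consecutive days.
- **Purpose (Abstract, Methods).** The three follow-up tests are there to evaluate the long-term impact of the program.

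**The concern.** The protocol states a scheduling principle and keeps to it in the first winter. The dates 18-24 December 2025 lie inside Washout 1 (24 November 2025 to 4 January 2026), which Table 1 marks as including the Christmas holiday. One year later the same calendar dates are the Follow-up 3 test window. The rule speaks of all assessments and makes no exception for follow-up.

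Two things are at stake. The first is completeness: children who are away cannot be tested in the kindergarten, and the limitations section already expects substantial loss at follow-up. The second is comparability. Accelerometer days outside school measure a different setting, so a change in activity between Post-test 4 and Follow-up 3 could partly reflect a change in the kind of day recorded. By follow-up every cluster is planned to have received all four conditions, so long-term impact is read largely from change over time, and a change of setting enters that reading.

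**Working it through.** **Inputs.** Dates and labels come from Table 1, the week numbers from the text beside it, and the 6-day wear requirement from Measurement of physical activity. The follow-up rows carry no year. They follow Post-test 4 (6-12 July 2026), so they are 2026. Week 1 starts on Monday 20 October 2025.

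**Step 1: reproduce the stated weeks.** Week *w* ends 7*w* − 1 days after 20 October 2025.

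| Stated week | Calendar week | Table 1 block ends | Agrees? |
|---|---|---|---|
| 38 | 6-12 Jul 2026 | 12 Jul (Post-test 4) | yes |
| 46 | 31 Aug-6 Sep 2026 | 6 Sep (Follow-up 1) | yes |
| 54 | 26 Oct-1 Nov 2026 | 1 Nov (Follow-up 2) | yes |
| 62 | 21-27 Dec 2026 | 24 Dec (Follow-up 3) | no |

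**Step 2: block lengths.**
- Follow-up 1, 13 July to 6 September: 56 days.
- Follow-up 2, 7 September to 1 November: 56 days.
- Follow-up 3, 2 November to 24 December: 46 days of washout + 7 days of test = 53 days. 53 / 7 = 7.57 weeks, 3 days short of 8 weeks.

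**Step 3: test windows.**
- Follow-up 1: Tuesday 1 to Sunday 6 September, 6 days, 4 weekdays.
- Follow-up 2: Monday 26 October to Sunday 1 November, 7 days, 5 weekdays.
- Follow-up 3: Friday 18 to Thursday 24 December, 7 days, 5 weekdays (18, 21, 22, 23 and 24 December), straddling weeks 61 and 62.

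The pre-tests and post-tests of Periods 1 to 4 are all Monday-Sunday weeks.

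**Step 4: exposure at Follow-up 3.** The holiday start is not given, so it is varied. A 6-day record begun on 18 December covers 18-23 December and contains one weekend (19-20 December). Non-school days = 2 weekend days + weekdays from 18 to 23 December that fall on or after the holiday start.

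| Assumed first holiday day | Test weekdays lost (of 5) | Non-school days in the 6-day record |
|---|---|---|
| 18 Dec | 5 | 2 + 4 = 6 |
| 19, 20 or 21 Dec | 4 | 2 + 3 = 5 |
| 22 Dec | 3 | 2 + 2 = 4 |
| 23 Dec | 2 | 2 + 1 = 3 |
| 24 Dec | 1 | 2 + 0 = 2 |
| 25 Dec | 0 | 2 + 0 = 2 |

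For comparison, six consecutive days inside an ordinary Monday-Sunday test week hold 1 non-school day (Monday-Saturday) or 2 (Tuesday-Sunday).

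**Step 5: alternative weeks for Follow-up 3.** Both are Monday-Sunday. The interval is counted from the end of Follow-up 2 on 1 November.
- 14-20 December: 49 days, 7 weeks (week 61). All five weekdays are kept if the holiday starts on 19 December or later, and one is lost if it starts on 18 December.
- 7-13 December: 42 days, 6 weeks (week 60). No weekday is lost under any start in the assumed range.

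**Step 6: slack at Follow-up 1.** Window length minus wear requirement = 6 − 6 = 0 days. If wear is kept within the window, every device must be on from 1 September. A 7-day window leaves 7 − 6 = 1 day.

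**The case against.** The strongest reply is that no lost test day is proved. The protocol says only late December. Ending the block on 24 December, three days short of 8 weeks, looks like an attempt to finish before Christmas. If the holiday starts on 25 December, no weekday is lost, and the accelerometer record holds 2 non-school days, as an ordinary test week can. This stands: the size of the problem is a range whose lower end is zero. It does not remove the conflict with the holiday rule or the 53-day block.

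A second reply is that the follow-up dates are common to all clusters, and that some change since Post-test 4 would be maturation in any week. This also stands. A reader might infer that the dates favour one condition, but the documents do not support that. The exposure concerns how complete the follow-up is and how its change over time is read.

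A reader might also infer that the protocol rules out September and that Follow-up 1 is therefore equally misplaced. It does not go so far. The remark about teachers concerns newly enrolled children and is used only to justify the start date, whereas trial children will have been attending since at least October 2025. That they would have unfamiliar teachers in September 2026, who would then rate them on the SCBE-30, is an inference. Follow-up 1 also observes the holiday rule in form, because the summer vacation precedes it.

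Finally, the protocol admits likely loss at follow-up and plans maximum likelihood for missing data. Neither addresses the dates, and neither makes holiday activity comparable with school-week activity.

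**Conclusion.** The point holds for Follow-up 3. Its test window lies in the period the protocol names for Christmas holidays, against the protocol's own rule for placing vacations. Separately, and under any holiday date, the block is 53 days rather than the labelled 56 and does not reach the end of week 62.

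The exposure is 0 to 5 of 5 test weekdays, and 2 to 6 non-school days in a 6-day accelerometer record begun on 18 December. Both ranges assume a holiday start between 18 and 25 December. The documents give no figure for the resulting dropout or distortion, so this is exposure to a risk and not a measured bias. It is worth changing because the change is cheap.

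Follow-up 1 is secondary. Its window has no slack for the wear requirement, opens straight after the summer gap, and falls in a month the protocol links to attrition. That calls for the passages to be reconciled. It does not show that the window is wrong.

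**What to change.** 1. Move the Follow-up 3 test to a full Monday-Sunday school week that ends before the holiday, once the kindergartens' closing dates are known. 14-20 December keeps a 7-week interval. 7-13 December gives 6 weeks and more margin.
2. Correct the 8-week label in Table 1 and the statements of 8-week intervals and week 62, so that table and text agree.
3. Analyse follow-up by actual days since Post-test 4 instead of nominal 8-week steps.
4. For Follow-up 1, reconcile the 1-6 September window with the protocol's remarks on that month, and say how 6 consecutive wear days will be obtained in a 6-day window. Moving this test is optional: a later week disturbs the 8-week spacing and may still fall in September.

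Cost: one test week is re-dated, and the last interval, already 3 days short, becomes 7 or 6 weeks. The test stays within six months of 12 July. No extra tests are needed.
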